#### Cognitive health counseling

All participants will receive a 15-minute session of cognitive health counseling in an individual face-to-face setting, including a take-home brochure (see Figs. 1 and 2). The counseling will inform about modifiable protective factors and risk factors for cognitive decline and dementia according to current research evidence. It will be based on the guidelines of the German Association for Psychiatry, Psychotherapy, and Psychosomatics on dementia. In particular, the counselors will explain protective effects of physical, cognitive, and social activities, and a Mediterranean diet. The counseling will further inform about the modifiable risk factors obesity, hypertension, diabetes mellitus, high cholesterol and homocysteine levels, smoking, and alcohol misuse.

In addition, the cognitive health counseling will comprise three telephone calls during the 5-week intervention period. In the first call (t_3_; week 1), participants will receive individual feedback based on their responses in the questionnaires on modifiable risk and protective factors at the pretest assessment. Here, we will give information about potential behavior changes and ask the participants whether they are motivated to adapt any of them. In the second and third telephone-based interview, we will ask for changes in behavior with respect to the predictive factors. Taken together, the behavior change techniques of the cognitive health counseling include the shaping of knowledge about cognitively healthy behaviors (t_2_), providing individual feedback on these behaviors (t_3_), and monitoring behaviors by the study staff with participants’ awareness (t_4_ and t_5_, cf. [48]).

#### Jigsaw puzzle intervention

Participants of the jigsaw puzzle group will solve jigsaw puzzles on 6 days a week for 5 weeks for at least 1 h per day. Every participant will get the same 300 piece jigsaw puzzle at first (*Beautiful Prague* by RSV; piece size: 2.45 × 2.4 cm). The participants will select subsequent puzzles out of a catalogue with 200, 300, 500, 1000, and 1500 piece jigsaw puzzles of the RSV adult puzzle 2016 collection (piece sizes included: 2.8 × 3.0 cm; 2.45 × 2.4 cm; 2.0 × 1.8 cm; 1.9 × 1.7 cm; and 1.8 × 1.7 cm, respectively).

The intervention will take place at participants’ homes. They will protocol their jigsaw puzzle time in a diary immediately after each jigsaw puzzle session. On each jigsaw puzzle day, participants will note the jigsaw puzzle name, the jigsaw puzzle duration, and if necessary additional comments about their experiences. Immediately after each of the three telephone-based cognitive health counseling sessions, participants will report the content of the diary for the monitoring of the protocol adherence and of the jigsaw puzzle performance (time per connected piece). Finally, the telephone-based interview includes questions about participants’ jigsaw puzzle experience for each solved jigsaw. Jigsaw puzzle experience will include the desire to solve the jigsaw puzzle, the pleasure in solving the jigsaw puzzle, the experienced competence of solving the jigsaw puzzle, and the perceived difficulty of the jigsaw puzzle. We will evaluate all four measures with a single question and a 5-point rating scale that ranges from “very high” to “not at all”. Participants will be able to freely choose their preferred jigsaw puzzles. However, we will recommend them to constantly increase the difficulty and challenge of the jigsaw puzzles through the increase of pieces per puzzle - which is accompanied with a decrease in piece size - as long as this does not reduce their pleasure and fun. These recommendations will depend on the reported perceived difficulty, challenge, pleasure, and fun, and their jigsaw puzzle performance (time per connected piece). If participants report adverse conditions associated with solving jigsaw puzzles (e.g., muscle pain during jigsaw puzzling or the development of a strong craving to solve jigsaw puzzles), the study staff will recommend to reduce puzzle time, not to stick to the protocol of at least 1 h per day, or to stop solving jigsaw puzzles as appropriate.

### Randomization

We will use stratified, blocked randomization to avoid baseline differences in age and cognitive status between the cognitive health counseling group and the jigsaw puzzle group, while at the same time achieving groups of similar sizes. We will stratify participants into two age bands (50–64 years and 65 years and older) and two cognitive status bands (MMSE: 24–27 and 28–30) resulting in four strata (stratum 1, age ≥ 64 years, MMSE 28–30; stratum 2, age ≥ 64 years, MMSE 24–27; stratum 3, age 50–64 years, MMSE 28–30; and stratum 4, age 50–64 years, MMSE 24–27). In each stratum, randomized allocation of the participants will happen in blocks of four (two participants to each group) using the online randomization software random.org (https://www.random.org/). [name] will generate the random allocation sequence for each stratum and conceal it in sequentially numbered opaque envelopes which we will store in a separate box for each stratum. [name], PF, and DL will conduct the telephone-based pre-screening. DL, [name], or HA will enroll participants after on-site assessment of the MMSE inclusion criterion and conduct the blinded assessment. [name] or PF will conduct the face-to-face cognitive health counseling. Immediately afterwards, they will disclose group assignment. Thus, the research staff responsible for enrollment and the first part of the cognitive health counseling will be blinded to group assignment and not able to predict future group assignment.

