## Methods

The Jigsaw *P*uzzles *A*s *C*ognitive *E*nrichment (PACE) study will take place at Ulm University, Germany, as a randomized, active-controlled, assessor-blinded superiority trial with two parallel groups. Between March and approximately October 2016, we will include and randomly assign 100 cognitively healthy, middle-aged and older adults (age 50 years and above) to a jigsaw puzzle group or a cognitive health counseling group with a 1:1 allocation ratio in blocks of four, stratified by cognitive status and age. Participants in the jigsaw puzzle group will engage in 30 days of solving jigsaw puzzles (6 days/week over a period of 5 weeks for at least 1 h/day) and receive cognitive health counseling (15-minutes face-to-face counseling plus three telephone calls). The cognitive health counseling group will receive the same counseling intervention but will not solve any jigsaw puzzles during the intervention period. The SPIRIT 2013 Checklist provides an overview about the contents of this study protocol (see Additional file 1).

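### The Randomization section puts 64-year-olds in two strata and, as a separate matter, says counselling staff cannot predict allocation although they disclose it in fixed blocks of four

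*Protocol article*

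**What the plan says.** All of this is in the protocol article.

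**Strata.** Randomization first sets "two age bands (50–64 years and 65 years and older" and two MMSE bands, 24–27 and 28–30. The same sentence then lists the four resulting strata. Strata 1 and 2 carry a lower age limit of 64, for example "stratum 1, age ≥ 64 years, MMSE 28–30". Strata 3 and 4 run up to and include 64, for example "stratum 3, age 50–64 years, MMSE 28–30". Each stratum has its own box of numbered opaque envelopes.

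**Blocks.** Methods describes allocation "with a 1:1 allocation ratio in blocks of four, stratified by cognitive status and age". Randomization adds that "randomized allocation of the participants will happen in blocks of four (two participants to each group").

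**Staff roles.** One set of staff enrols participants after the on-site MMSE and carries out the blinded assessments. Two other people share the face-to-face counselling. Of these two the section says: "Immediately afterwards, they will disclose group assignment". Procedure describes the staff who disclose as not blinded. At least one of the two also takes part in telephone pre-screening.

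**Assurance.** Randomization concludes that the staff responsible for enrolment, and also those giving the first part of the counselling, will be "blinded to group assignment and not able to predict future group assignment".

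**The concern.** The strata decide which envelope sequence a participant is drawn from. If two strata claim the same person, the written rule does not fix the sequence, and the strata used in the trial may differ from those reported.

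The assurance about prediction is presented as a consequence of the procedure, but for the counselling staff the procedure points the other way. Someone who discloses allocations learns them. With a known fixed block size, the earlier allocations in a stratum partly or wholly determine the next one. Before a session that counsellor may be blinded in the sense of not having seen the envelope, yet still know what it contains.

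What is at stake is the neutrality of the session before disclosure. The section on blinding and expectation effects relies on shared counselling, and on even-handed statements made before disclosure, to create similar expectations in both groups. A counsellor who foresees the arm could, even without intent, deliver that session differently.

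**Working it through.** The plan gives no figure for predictability, so there is none to reproduce. The stated 90% power does not enter this point.

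**1. Strata side by side**

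- Age 64, MMSE 28–30: the bands give stratum 3 only; the stratum definitions give strata 1 and 3.
- Age 64, MMSE 24–27: the bands give stratum 4 only; the stratum definitions give strata 2 and 4.
- Any other age: bands and strata agree.

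The documents give no age distribution. Assuming whole years of age spread evenly, the share aged 64 is 1/26 = 3.8% over 50–75 and 1/31 = 3.2% over 50–80. That is about 3 to 4 of the planned 100.

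**2. Predictability in fixed blocks of four**

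Inputs: block size four, two per group, within stratum (Methods and Randomization). Assumption: the discloser knows the block size and every earlier allocation in that stratum. The protocol states the block size and describes no masking of it.

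A 2:2 block has 6 possible orders, hence 6 × 4 = 24 positions.

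- Fourth position: always certain, 6 of 6.
- Third position: certain only when the first two match, 2 of 6.
- First and second positions: never certain.

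Share certain = (6 + 2)/24 = 8/24 = 33.3%.

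Probability that the best guess is right, by position:

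- First: 1/2 = 0.500.
- Second (guess the other arm): 4/6 = 0.667.
- Third: 1/3 × 1 + 2/3 × 1/2 = 0.667.
- Fourth: 1.000.

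Average = (0.500 + 0.667 + 0.667 + 1.000)/4 = 0.708, against 0.500 by chance.

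**3. What varied block sizes would change**

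This was simulated with equally likely sizes, 24 allocations per stratum (an assumption) and 4,000 repetitions. The guesser knows the set of sizes but not their order, and guesses optimally.

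- Fixed four: 33% certain, best guess right 71%.
- Sizes 4 and 6: about 6% certain, best guess right about 69%.
- Sizes 2, 4 and 6: about 4% certain, best guess right about 70%.
- Sizes 4, 6 and 8: about 2% certain, best guess right about 67%.

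Varied blocks remove most of the certainty but little of the guessing advantage. A counsellor with no knowledge of past allocations is back at 50%.

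**The case against.** The age limit reads as a slip. The bands in the same sentence do not overlap and place age 64 in strata 3 and 4, few people are affected, and allocation within either stratum is still random. This stands as a limit on the consequence, but the stratum list is the rule that staff would apply, and it is wrong as printed.

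A reader might infer that the overlap makes allocation predictable, or that staff could pick a favourable box for a 64-year-old. The documents support neither. The overlap adds nothing to block predictability, and the article says who discloses, not who opens the envelope or chooses the box.

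A reader might also infer biased enrolment. That is remote. Blinded assessors enrol, and nothing shows that they can predict. A discloser who pre-screens by telephone does so before the MMSE is measured, so the stratum is not yet known. Nor is the person's place in the block. Pretest precedes counselling, so baseline scores are untouched.

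It is equally tempting to say that uneven counselling goes straight into the group contrast. Both groups receive the counselling. Only one 15-minute session, with a brochure, precedes disclosure, and the three telephone calls follow it. The Discussion names differential counselling effects as a limitation, and Statistical analysis plans additional analyses that adjust for changes in activities and diet. Outcome assessors stay blinded. All of this limits the harm.

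Finally, two people share disclosure, so either may hold only part of a stratum's history. The 33% and 71% are therefore upper figures. None of these points rescues the assurance for the counselling staff.

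**Conclusion.** Two separate statements in Randomization are wrong as written.

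1. The stratum definitions contradict the age bands. This affects only people aged exactly 64, about 3 to 4 of 100 under the assumption of evenly spread ages.
2. The assurance about prediction does not follow for the staff who give the first counselling session. With full knowledge of a stratum's history they are certain of up to 1/3 of allocations and guess up to 71% correctly. Both figures are lower if the two disclosers do not share what they know.

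The documents do not show that the enrolling assessors can predict allocation, so the assurance may stand for them. The main risk is uneven delivery of the single session before disclosure. Biased eligibility and a large direct effect on the group comparison are not supported. Removed names prevent a full tracing of who holds which role.

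**What to change.** **Strata.** Define strata 1 and 2 as age 65 or above, matching the bands, in the text and on the envelope boxes. For any 64-year-old already randomised, list the stratum used. This costs a wording change, new labels and a short listing.

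**Disclosure.** Have an existing staff member other than that participant's counsellor open the envelope and disclose. This is the main remedy. It works fully only if the counsellor does not learn earlier allocations another way, for example by disclosing for a colleague or making the later telephone calls. It needs no extra staff, only some scheduling.

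**Blocks.** For allocations still to come, use varied block sizes known only to the person who generates the list, for example 4 and 6. This cuts certain allocations from 33% to about 6% but leaves the best guess at about 69%, so it supplements the change in disclosure and does not replace it. The cost is regenerated lists and slightly looser balance within strata.

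**If enrolment is complete** (Methods plans inclusion from March to about October 2016). Limit the assurance to the enrolling assessors and report the residual predictability for the counselling staff, including whether the two disclosers shared allocation history. This costs wording only.

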### Participants

The study aims to include 100 participants who we will recruit via local newspaper articles and flyers. Inclusion criteria are 50 years of age or older, unimpaired cognition defined by a Mini-Mental State Examination (MMSE) [27] score ≥ 24, the commitment to invest at least 1 h per day for 30 days in solving jigsaw puzzles within a 5-week period, an interest in solving jigsaw puzzles, and low jigsaw puzzle experience in the past 5 years (fewer than five completed jigsaw puzzles).

Exclusion criteria are the participation in another interventional study and self-reported, uncorrected impairment in vision (e.g., red-green color blindness) or motor function of the upper extremity (e.g., hand tremor) that considerably impairs jigsaw puzzle performance. In addition, individuals with any self-reported psychiatric, neurological, or other diseases that could affect cognitive change over time will be excluded. These diseases comprise current major depression, dementia or Parkinson’s disease, a history of stroke with current impairment, epilepsy, multiple sclerosis, or a current malignant tumor. Apart from the cognitive impairment, which we will assess at the on-site screening (t_2A_), telephone-based pre-screening will examine inclusion and exclusion criteria after oral informed consent (t_1_, see Figs. 1 and 2).

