## Discussion

Our upcoming findings might have a clinical implication for adults over 50 years of age who have low puzzle experience in the past 5 years but are interested in solving jigsaw puzzles. As solving jigsaw puzzles depicts a low-cost, intrinsically motivating leisure activity, which can be executed alone or with others, and without the need to operate a digital device, positive results would indicate a highly feasible cognitive intervention to improve visuospatial cognition and everyday functioning, and psychological outcomes in this population. We will not investigate the effect of jigsaw puzzling on overall cognitive functioning including cognitive domains such as language or verbal working memory as generalization to non-trained cognitive domains cannot be expected from a theoretical and an empirical point of view [56, 57]. However, as visuospatial dysfunctions (e.g., deficits in visuoconstruction or visuospatial episodic memory and missed traffic signs or relocated objects) are common in neurocognitive diseases such as mild cognitive impairment and dementia - especially due to Alzheimer’s disease, dementia with Lewy bodies, and posterior cortical atrophy [23] - lifelong jigsaw puzzle experience might be one out of many cognitive activities that may contribute to a delayed clinical manifestation of neurocognitive disorders.

Limitations of the study design are the lack of a long-term follow-up and of the investigation of biological mediators, and the lack of participants’ blinding to group allocation, which could lead to differential expectation effects. In addition, the selected outcomes may have limitations in assessing the effects of jigsaw puzzling on cognitive abilities and daily functioning. Finally, the cognitive health counseling might have different behavioral effects in the counseling and the puzzle group that could mask the effects of jigsaw puzzling.

To address the lack of long-term follow-up, we will ask participants after study completion whether they will be interested in future long-term follow-up that we aim to conduct approximately 1.5 years after posttest assessment.

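### Two members of one household can enrol and be allocated to different arms, so a control may live with the puzzles, which can dilute the primary contrast

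*Protocol article*

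**What the plan says.** All references are to the protocol article.

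- **Recruitment and eligibility (Participants).** "The study aims to include 100 participants who we will recruit via local newspaper articles and flyers". The inclusion list requires, of both future arms, "an interest in solving jigsaw puzzles, and low jigsaw puzzle experience in the past 5 years", together with a commitment of an hour a day for 30 days. The exclusion list opens with "Exclusion criteria are the participation in another interventional study and self-reported, uncorrected impairment in vision" and continues with diseases that could affect cognition. Neither list mentions a second participant from the same household.
- **Allocation (Methods, Randomization).** Individuals are allocated "with a 1:1 allocation ratio in blocks of four, stratified by cognitive status and age". Within each stratum, "randomized allocation of the participants will happen in blocks of four (two participants to each group". There are four strata (two age bands by two MMSE bands), and no rule for couples.
- **Setting (Jigsaw puzzle intervention).** "The intervention will take place at participants’ homes", on 6 days a week for 5 weeks. The Discussion describes puzzling as a leisure activity "which can be executed alone or with others".
- **Safeguard for controls (Interventions).** The counseling group is asked to refrain from puzzles during the 5 weeks.
- **Monitoring (Procedure, Jigsaw puzzle intervention).** The diary and the adherence questions in the calls are described for the jigsaw group only.
- **Analysis (Statistical analysis).** The primary analysis keeps participants in the arm to which they were allocated.

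**The concern.** Two partners who answer the same notice can both qualify and are then allocated separately. If they are split, the control lives for five weeks with the puzzles and with someone who solves them for at least an hour on most days. That control was selected for wanting to puzzle and had agreed to give it the time. The only barrier described is a request to abstain.

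A control who joins in still counts as a control, so any benefit gained shrinks the group × time contrast in global visuospatial cognition. A null result could then not be told apart from contamination. The supportive per-protocol analysis would not detect it, because its criterion is completed puzzle days and nothing is stated about controls who puzzled.

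**Working it through.** **Inputs from the document (Power analysis).** 50 per group, 15% dropout, f = 0.1, pretest–posttest correlation r = 0.85, α = 0.05, stated power 90%.

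**Step 1: reproduce the stated power.** For the within-between interaction in a repeated-measures ANOVA with m = 2 occasions, λ = f² × N × m / (1 − r), with 1 and N − 2 degrees of freedom. With N = 100 × 0.85 = 85:

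λ = 0.01 × 85 × 2 / 0.15 = 11.33, which gives power 91.4%.

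N = 84 gives 91.1% and N = 86 gives 91.7%. The stated 90% is therefore reproduced, and the power statement contains no error.

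**Step 2: how often a couple is split.**

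- *Same block of four:* once one partner holds a slot, three remain and two of them belong to the other arm, so the probability is 2/3.
- *Different blocks or strata:* the allocations are independent at 1:1, so the probability is 1/2. This covers couples who differ in age band or MMSE band.

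Each enrolled couple therefore yields on average 0.50 to 0.67 controls who live with a jigsaw participant.

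**Step 3: dilution.** Let k be the number of couples, p the split probability and u the share of the puzzle effect that an exposed control takes in. The diluted share of the control arm is c = k × p × u / 50, and the expected effect becomes f × (1 − c). For example, k = 5, p = 1/2 and u = 1 give c = 2.5/50 = 5%, f = 0.095 and power 88.5%.

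The document gives neither k nor u, so both are assumptions. In each range below, the first figure uses p = 1/2 and the second p = 2/3, with N = 85.

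| Couples (k) | Exposed controls, expected | c at full uptake | Power, full uptake | Power, half uptake |
|---|---|---|---|---|
| 0 | 0 | 0% | 91.4% | 91.4% |
| 2 | 1.0–1.3 | 2.0–2.7% | 90.3–90.0% | 90.9–90.7% |
| 5 | 2.5–3.3 | 5.0–6.7% | 88.5–87.4% | 90.1–89.6% |
| 10 | 5.0–6.7 | 10.0–13.3% | 85.0–82.2% | 88.5–87.4% |

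The 82.2% corner needs 10 couples, every couple in a single block, and every split control taking in the whole effect.

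**The case against.** The strongest reply is that nothing in the article is stated wrongly. A household rule may stand in the full protocol or on the screening form, and no text says that couples enrolled. Eligibility also narrows the pool: both partners must be 50 or over, interested, of low recent puzzle experience, free of the listed diseases and willing to give an hour a day. Sharing a home has no effect unless the control actually puzzles. Controls are asked not to, and they are telephoned three times. The additional analyses adjust for change in cognitive activities.

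Much of this stands. It makes the point conditional and its size unknown. It does not close the gap. The eligibility lists are presented as the criteria and admit both partners. The activity questionnaire asks whether each of 44 activities was done at least once in the past 4 weeks, not for how long, and the article does not say that jigsaws are among them. Adjusting for activity after randomisation would in any case not restore the randomised contrast.

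A reader might infer three stronger points, which the document does not support:

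- **That control partners are the likeliest to unblind assessors.** Every participant knows the allocation. The section on blinding provides reminders at the last call and just before the posttest, with a signed confirmation. Nothing singles out partners.
- **That analysing partners as independent is a defect.** Couples are split with probability 1/2 to 2/3. A positive within-pair correlation lowers the variance of the group difference when a pair is split and raises it when the pair shares an arm. On average, ignoring the pairing is neutral or conservative.
- **That contamination will occur, or that the power figure is wrong.** The first depends on behaviour that the document cannot predict, and the second is contradicted by Step 1.

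**Conclusion.** The point holds as a low-severity design improvement. The article's eligibility and allocation rules let two household members be placed in different arms. Because the intervention is solved at home by people chosen for their interest, a control can be exposed despite the request to abstain. Any puzzle benefit gained in this way moves the primary comparison toward no effect.

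The size rests on an assumed number of couples and an assumed uptake. A few couples would cost roughly 1 to 4 points against the recomputed 91.4%. The loss reaches about 6 to 9 points only with 10 couples and full uptake. Confidence that this affects the result is low, but prevention costs almost nothing.

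**What to change.** Add to the Participants section that only one person per household may enrol, and check this with one question at the existing telephone pre-screening. The downside is the loss of a few interested partners during recruitment. The rule closes the household route only, since a control could still obtain a puzzle elsewhere.

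Giving the second partner the first partner's arm without drawing an envelope should not be used as a substitute. That allocation would be known before enrolment, which undoes the concealment described under Randomization.

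If enrolment has already closed, identify shared households, ask controls about puzzling, and report a sensitivity analysis that leaves out controls who lived with a jigsaw participant.
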